## Abstract

**Background:**

Hypertension and diabetes represent the first and third highest contributors to global disability. While mobile health (mHealth) messaging programs have rapidly increased in low- and middle-income countries (LMIC), adaptations for specific patient health needs is a new approach to manage chronic conditions.

**Objective:**

The primary aim of this study is to develop and test an mHealth communication intervention using electronic data capture (by tablet) and voice messaging to improve hypertension and diabetes self-management in Cambodia. The secondary aim is to share results with the Cambodian Ministry of Health and development partners to inform health policy and develop strategies for hypertension and diabetes control.

**Methods:**

The study design is a cluster randomized controlled clinical trial randomizing each of 75 Community peer educators (PEs), trained and coordinated by MoPoTsyo Patient Information Center in Phnom Penh, into one of 3 groups of 25 (approximately 60 patients each) to receive either tablet+messages, tablet only, or no intervention (control). The total sample within each group includes 25 clusters and approximately 1500 patients located in 7 Operational Districts in rural regions or urban slums in Cambodia. The interventions (groups 1 and 2) were compared with usual PE monitoring without the tablet or mHealth messaging interventions. Focus groups and informant interviews were conducted to develop messages according to specific themes—medications adherence, laboratory testing, physician visits, obesity, smoking, and general lifestyle issues. Using the data received at monthly PE monitoring meetings, patients will receive specific messages based on their individual health challenges. Following the intervention completion, clinical and process outcomes will be compared with baseline metrics between groups.

**Results:**

PEs were randomized in July 2017, and the intervention was implemented in September 2017 through June 2018. Analyses are underway.

**Conclusions:**

This project is unique in its combination of electronic data transfer, which can be accessed immediately, with voice messages most relevant to individual patients’ needs. Positive results will indicate the value of using targeted messaging in patient-specific, self-management issues to improve hypertension and diabetes control.

**International Registered Report Identifier (IRRID):**

DERR1-10.2196/11614

## Introduction

The incidence and prevalence of cardiovascular disease and its risk factors, including hypertension and diabetes mellitus, is increasing rapidly in low- and middle-income countries (LMIC) [1-3]. After the turn of the century, epidemiological trends emerged that were characterized by a major shift in the size and relative magnitude of many risk factors for mortality and disability. High systolic blood pressure and high fasting plasma glucose increased steadily in impact on the global burden of disease [4]. Between 1990 and 2015, systolic blood pressure increased across the globe with associated increases in both mortality and disability [5]. In 2015, the top 3 greatest contributors to global disability-adjusted life-years among level 3 risks were high systolic blood pressure, smoking, and high fasting plasma glucose [6]; these increases are noteworthy as their sequelae, heart disease and stroke, are now the leading cause of death in these nations [7]. In Cambodia, it has been estimated that more than half (52.0%) of the total diabetic population is untreated, and despite treatment, only 24% of all diabetes is adequately controlled [8]. Poverty, inequality, lack of education, along with the nature of the nutritional transition, are root causes of the problem while limited resources mean that noncommunicable diseases (NCDs) must compete for political attention and financial investment. The global trend of increasing risk factors for cardiovascular diseases will continue unless effective methods are implemented to not only identify high-risk individuals but also implement effective and sustainable lifestyle and pharmacological interventions [9]. Tools and interventions to improve the self-management of cardiovascular disease risk factors, such as hypertension and diabetes, are greatly needed in community settings where health care resources may be limited.

Mobile health (mHealth) messaging programs have rapidly increased in LMIC and provide a means to support self-management programs especially needed for NCDs. A number of studies have focused on short message service (SMS) text messaging to improve outcomes for hypertension [10,11] and diabetes [11,12-14]. While these studies have generally shown messaging to be an acceptable format to participants, results have been mixed, with several showing small changes in some disease outcomes [10,12-14] or behavioral change [11,15]. However, no consistent patterns between intervention and control groups have been found. While mHealth messaging systems in the literature have varied in terms of features provided, the evaluation of targeting patients with voice messages to address individualized problems has been limited.

This study aims to leverage the activities of a Cambodian nongovernmental organization, MoPoTsyo Patient Information Center, to test if improvement of data transfer using electronic data capture combined with sending targeted voice messages to patients, would improve outcomes for hypertension and diabetes. As peer educators (PEs) were already established in the MoPoTsyo system to monitor hypertension and diabetes across the country, it provided us with the opportunity to both increase the time from patient measurement to data utilization (through e-tablets) and to use these data to individualize messages targeting specific issues revealed from the data (voice messages).

The primary aim of this study is to develop and test an mHealth communication intervention using electronic data capture and voice messaging to improve hypertension and diabetes self-management in Cambodia by implementing a combined electronic health (eHealth) and mHealth intervention. The secondary aim is to share results with the Cambodian Ministry of Health and development partners to inform health policy and develop strategies for hypertension and diabetes control.

## Methods

### Human Subjects Approval

This is a randomized controlled clinical trial to test an intervention comprising faster data capture plus targeted voice messages compared with PE monthly monitoring in a community-based sample in Cambodia for improvement of hypertension and diabetes outcomes. This study received Institutional Review Board approval from the University of Washington Division of Human Subjects and the National Ethics Committee for Health Research in Cambodia. All PEs, regardless of study allocation, and participants assigned to the telephone message intervention provided written informed consent. Informed consent from community participants who did not receive mHealth messages were waived by the Institutional Review Boards as routine monitoring provided study outcome data for these groups. This study was determined to not qualify as an “Applicable Clinical Trial” according to the National Institutes of Health definition [16] at the time it was initiated and, thus, was not registered in clinicaltrials.gov. As the risk of harm is minimal in this study, no criteria for discontinuation were developed. An Advisory Committee comprising Cambodian Ministry of Health officials, health care providers, and technology experts was convened to provide oversight and guidance to the study.

### Study Setting

In Cambodia, where greater life expectancy is causing rapid increases in NCDs [17], nongovernmental organizations have stepped in when government programs have not been able to address disease locally. MoPoTsyo Patient Information Center is a Cambodian nongovernmental organization for people with chronic disease in Cambodia [18]. It was established in 2004 to provide an institutional and practical response to the information and care needed by patients with hypertension and diabetes. Their model recruits and involves patients as volunteers and trains them to provide counseling on NCDs and monitor key health indicators over time. PEs see patients on a monthly basis to reinforce training and monitor key metrics, including blood pressure, glucose, weight, and adherence to medications. Patients keep paper logs of their health information that are updated at each PE visit. Currently, logs summaries are transferred to the MoPoTsyo Patient Information Center for manual entry and to update patient histories. Since 2005, MoPoTsyo has trained >200 PEs who have registered >31,000 patients in 7 rural provinces and poor urban slum areas of Phnom Penh. Patient and pharmacy records have been used to document the success of the program showing dramatic improvement in chronic disease management [19].

Seven Operational Districts (ODs) representing rural geographic regions or urban slums were selected for inclusion in the project; these included 4 ODs in Kampong Speu province, 2 ODs in Kampong Thom province, 1 OD in Kampong Cham province, and the municipality of Phnom Penh. This area includes 87 PEs who were included for simple randomization (by computer-generated random numbers) into the 3 arms of the study. All patients registered into the MoPoTsyo Patient Information Center system at the time of PE randomization were included as the community sample to receive mHealth messages with no exclusion criteria. Owing to the nature of this intervention, it was not possible to blind participants to study allocation. However, as patients of PEs were clustered geographically, there was a minimum chance of patients interacting across clusters to discuss the study.

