### Approach

In this study, we are collaborating with MoPoTsyo Patient Information Center to enhance their Peer Educator Network model through the application of mHealth-tailored phone messaging and improved eHealth communication throughout the system. A focus on hypertension, justified by the extremely low medication adherence of hypertensive patients compared with diabetic patients, shifts the intervention to an area of great need. Two interventions will be tested, one at the PE level and one at the patient level. The first includes providing electronic tablets to PEs for data collection and transfer to the MoPoTsyo database in Phnom Penh. The tablets are intended to speed up data collection and entry, reduce paper, increase accuracy, and eliminate lengthy distances that must be traveled to bring paperwork to MoPoTsyo. In addition, the tablets will allow PEs to scan a patient’s record “handbook” (log kept with the patient) to be verified by MoPoTsyo quality control staff should data appear suspicious. At the patient level, voice messages developed to address specific patient problems (eg, uncontrolled blood pressure or glucose, medications not picked up at the pharmacy, weight gain, etc) will be sent to patients based on the data received from the monthly visits to the PE. This study has randomly selected 75 PEs for assignment to 1 of 3 intervention groups—tablet+messaging, tablet only, or control (no tablet or voice messages). Figure 1 shows the study design. As we estimate that each of the 25 PEs in each group monitors about 60 patients, each arm of the study will include about 1500 participants for a total community sample of about 4500.

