### Electronic Data Capture

Fifty PEs (25 in the tablet+messaging group and 25 in the tablet only group) received a 12-inch Chuwi Hi12 Tablet with touchscreen compatible for Windows 10-Android 5.1 to record patient information each month. Data are entered online or offline during the patient visit with backup recorded in the patient handbook (log). Data are transferred to the MoPoTsyo database stored on a Dell PowerEdge T630 Server, RAM 32GB (Gigabytes), HDD 4TB, (hard disk 4 Terabytes), speed 2.4 GHz, Cache 20MB. The operating system is Windows Server 2012R2 with database application Microsoft SQL server 2014. Initial training has been provided by MoPoTsyo staff to assure PEs are comfortable with using the tablets for their monthly monitoring visits. It has become clear, perhaps because of their older age and lack of experience, that many of the PEs are challenged by the technical aspects of this new tool. We have begun weekly Web-conferences (broadcast on the tablets) to help address problems and increase PE skills in tablet use. In addition, pharmacies have received tablets to input prescriptions and provide information to MoPoTsyo regarding invoices when medications are purchased. We do not anticipate significant dropout of PEs based on historical experience. PEs seldom leave MoPoTsyo unless illness or death intervenes. Retention efforts for community participants include the free health monitoring provided by PEs and the social interactions that result in this popular program. PEs in all groups are coached to be vigilant in responding to patient questions and needs as well as to contact the MoPoTsyo Center with any issues that arise.

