#### Power

We will conduct the primary analysis evaluating mean differences of change in study outcomes by PE group assignment. With a sample of 50 (PE pairwise comparisons between the 2 intervention groups and controls) assuming an alpha of.05 and improvements of controls at a rate similar to 12-month change previously seen, we have 94% power to assess a 50% greater improvement in systolic blood pressure in the intervention group, and 79% power to assess a 40% greater improvement. We will have >99% power to detect differences in efficacy analyses. We believe that these are realistic goals based on results of other rigorous mHealth studies in LMIC [24]. Power calculations were completed using STATA (StataCorp College Station).

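### The article puts 87 peer educators into the randomisation in one place and works with 75 (25 per arm) everywhere else, and does not account for the other 12

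*Protocol article*

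**What the plan says.** All references are to the protocol article.

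- **Study Setting:** "This area includes 87 PEs who were included for simple randomization (by computer-generated random numbers) into the 3 arms of the study". The same section takes in every patient registered when the PEs were randomised and applies no exclusion criteria.
- **Abstract, Methods:** the design is described as "randomizing each of 75 Community peer educators (PEs" and so on, "into one of 3 groups of 25 (approximately 60 patients each".
- **Approach:** "This study has randomly selected 75 PEs for assignment to 1 of 3 intervention groups", with 25 PEs in each group, about 1500 participants per arm and about 4500 in total.
- **Electronic Data Capture:** "Fifty PEs (25 in the tablet+messaging group and 25 in the tablet only group) received" a tablet.
- **Power:** the calculation is made "With a sample of 50" PEs per pairwise comparison.
- **Statistical Analyses:** an intention-to-treat comparison is promised on PE-level change, and again in the patient-level models.
- **Abstract, Results:** "PEs were randomized in July 2017", so the allocation was already fixed when the article was written.

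**The concern.** The PE is the unit of randomisation and also the unit of the primary comparison. The patient population is tied to the PEs as well, since it is everyone registered at the time the PEs were randomised. The list of randomised PEs therefore defines the intention-to-treat set at both levels, and the article gives that list two different lengths.

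If all 87 were allocated and only 75 carried forward, 12 clusters left after allocation. The comparison would then no longer be intention-to-treat, and whatever decided which PEs left could bias it. If instead 75 were drawn first and then split, the intention-to-treat set is intact and only the Study Setting sentence is wrong. A reader of the article cannot be sure which happened.

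There is also a smaller mismatch of terms. Simple randomisation, in its usual sense of independent assignment of each unit, does not fix the arm sizes, whereas three arms of exactly 25 imply a fixed-size allocation.

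**Working it through.** **Inputs.** 87 PEs (Study Setting); 75 PEs in 3 groups of 25 (Abstract, Approach); 25 + 25 tablets (Electronic Data Capture); about 60 patients per PE (Abstract, Approach); 50 PEs per comparison (Power).

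**1. The article's own totals follow from 75.**
- PEs: 3 × 25 = 75.
- Patients per arm: 25 × 60 = 1500, as stated.
- All patients: 75 × 60 = 4500, as stated.
- Tablets: 25 + 25 = 50, as stated.
- PEs per pairwise comparison: 25 + 25 = 50, as stated.

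**2. None of them follows from 87.**
- Equal arms would be 87 / 3 = 29, not 25.
- All patients would be 87 × 60 = 5220, not 4500.

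**3. Size of the gap.**
- 87 − 75 = 12 PEs.
- 12 / 87 = 13.8%.
- 12 × 60 = about 720 patients.

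**4. What could have happened, set against the text.**

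| Sequence | Fits | Conflicts with | Intention-to-treat set |
|---|---|---|---|
| 75 drawn from 87, then split 25/25/25 | Abstract, Approach, Electronic Data Capture, Power | Study Setting, which takes all 87 into the arms | 75 PEs, intact |
| 87 allocated, 12 then left out | Study Setting, and the later counts of 25 | Abstract and Approach, which give 75 as the number randomised or selected | 87 PEs, broken if only 75 are analysed |
| 87 allocated, none left out, 50 given tablets | Study Setting, Electronic Data Capture | Approach: 87 − 50 = 37 controls, not 25 | 87 PEs |

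Every row conflicts with at least one section, so at least one statement is wrong.

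**5. The label.** Under independent assignment of 75 PEs with probability 1/3 each,

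P(25, 25, 25) = 75! / (25!³ × 3⁷⁵) = 0.0109, about 1.1%.

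This shows only that the word and the arm sizes do not match. It says nothing about the quality of the allocation actually used.

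**The case against.** The strongest reply is that the article already contains the reconciling reading. The Approach section's wording, "This study has randomly selected 75 PEs for assignment to 1 of 3 intervention groups", implies a larger pool, and Study Setting, where the 87 appears, is describing the area. On that reading 87 PEs were available and 75 were drawn. The Abstract also gives 75 as the number randomised, the tablet count is reported as done, and Electronic Data Capture expects little PE dropout. This stands as far as it goes and makes the benign sequence the more likely one. It does not remove the Study Setting sentence, which puts the 87 into the arms and not merely into the area.

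The second reply is that the word simple may have meant only unstratified. Ordering one list by random number and taking 25, 25 and 25 would fit the mention of computer-generated numbers. That is fair: the mislabel is mostly terminology, and no bias is shown to follow from it. Since the two tablet arms are reported as exactly 25 each, it would also be wrong to infer that the real arms were uneven.

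A reader might go further and infer that the power is undermined. The documents do not support this.

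- The basis of 25 per arm is used consistently in the Abstract, Approach, Electronic Data Capture and Power sections.
- The article gives neither the control change nor the PE-level SD, so 94% and 79% cannot be derived from it. They can be checked against each other, assuming a two-sided t test at 0.05 with 25 versus 25. The effect that gives 94% is 1.015 SD. Multiplied by 40/50 it is 0.812 SD, with power 80.3%, close to the stated 79%. Starting from 79% (0.799 SD) and multiplying by 50/40 gives 93.3%, close to 94%.
- With 29 versus 29 the same effects give 96.7% and 85.9% (anchored on the 94%), or 96.2% and 84.8% (anchored on the 79%). Randomising 87 in equal arms would make the stated power slightly conservative.

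**Conclusion.** The contradiction is real. The number of randomised clusters is wrong in at least one place, and 12 PEs, with about 720 patients if the average of 60 holds for them, are unexplained.

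The consequence for intention-to-treat is conditional. It arises only if all 87 were allocated and 12 were then left out. A reader might infer that this happened, but no section reports a PE being removed after allocation, and the Approach wording points the other way.

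This is an inconsistency of reporting that should be settled before the results are reported. It is not a demonstrated flaw in the design, the allocation or the power.

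**What to change.** From the randomisation list, correct the Study Setting sentence to state how many PEs were available, how many were selected and how many were allocated to each arm. Say whether the 12 fell out before or after allocation.

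- **If 75 were drawn from 87 and split 25/25/25:** say so, and replace the word simple with a description of the fixed-size allocation used.
- **If 87 were allocated:** analyse all 87 PEs and their registered patients in their assigned arms, report the arm counts, and restate the cluster and patient numbers wherever 75, 25 and 4500 appear.

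In the first case the cost is a text correction. In the second, data for the 12 further PEs must be added. Outcomes for PEs without the intervention come from routine monitoring (Human Subjects Approval), so those data should largely exist. The Results section says data are still being cleaned and analysed, so either correction can be made before the analysis set is closed.

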### Approach

In this study, we are collaborating with MoPoTsyo Patient Information Center to enhance their Peer Educator Network model through the application of mHealth-tailored phone messaging and improved eHealth communication throughout the system. A focus on hypertension, justified by the extremely low medication adherence of hypertensive patients compared with diabetic patients, shifts the intervention to an area of great need. Two interventions will be tested, one at the PE level and one at the patient level. The first includes providing electronic tablets to PEs for data collection and transfer to the MoPoTsyo database in Phnom Penh. The tablets are intended to speed up data collection and entry, reduce paper, increase accuracy, and eliminate lengthy distances that must be traveled to bring paperwork to MoPoTsyo. In addition, the tablets will allow PEs to scan a patient’s record “handbook” (log kept with the patient) to be verified by MoPoTsyo quality control staff should data appear suspicious. At the patient level, voice messages developed to address specific patient problems (eg, uncontrolled blood pressure or glucose, medications not picked up at the pharmacy, weight gain, etc) will be sent to patients based on the data received from the monthly visits to the PE. This study has randomly selected 75 PEs for assignment to 1 of 3 intervention groups—tablet+messaging, tablet only, or control (no tablet or voice messages). Figure 1 shows the study design. As we estimate that each of the 25 PEs in each group monitors about 60 patients, each arm of the study will include about 1500 participants for a total community sample of about 4500.

### Electronic Data Capture

Fifty PEs (25 in the tablet+messaging group and 25 in the tablet only group) received a 12-inch Chuwi Hi12 Tablet with touchscreen compatible for Windows 10-Android 5.1 to record patient information each month. Data are entered online or offline during the patient visit with backup recorded in the patient handbook (log). Data are transferred to the MoPoTsyo database stored on a Dell PowerEdge T630 Server, RAM 32GB (Gigabytes), HDD 4TB, (hard disk 4 Terabytes), speed 2.4 GHz, Cache 20MB. The operating system is Windows Server 2012R2 with database application Microsoft SQL server 2014. Initial training has been provided by MoPoTsyo staff to assure PEs are comfortable with using the tablets for their monthly monitoring visits. It has become clear, perhaps because of their older age and lack of experience, that many of the PEs are challenged by the technical aspects of this new tool. We have begun weekly Web-conferences (broadcast on the tablets) to help address problems and increase PE skills in tablet use. In addition, pharmacies have received tablets to input prescriptions and provide information to MoPoTsyo regarding invoices when medications are purchased. We do not anticipate significant dropout of PEs based on historical experience. PEs seldom leave MoPoTsyo unless illness or death intervenes. Retention efforts for community participants include the free health monitoring provided by PEs and the social interactions that result in this popular program. PEs in all groups are coached to be vigilant in responding to patient questions and needs as well as to contact the MoPoTsyo Center with any issues that arise.

